# The effect of low-intensity pulsed ultrasound (LIPUS) for the treatment of upper and lower extremity non-union compared to surgical intervention (PiNGUin): study protocol for a national, prospective, randomized controlled, open-label, multicenter, non-inferiority study

**DOI:** 10.1186/s13063-025-09212-y

**Published:** 2025-10-27

**Keywords:** Non-union, Low-intensity pulsed ultrasound (LIPUS), Medical device, Fracture healing, Randomized controlled trial (RCT), Non-inferiority study

## Abstract

**Background:**

Non-unions, defined as fractures not healed after at least 6 months, are a multifactorial complication occurring in 2–10% of all fractures and in up to 30% of patients with certain risk factors. Treatment costs are markedly higher than those associated with normal fracture healing and patients often suffer from pain and loss of function. Surgical revision is the gold standard for treatment; however, the disadvantages are re-hospitalization, possible secondary diseases and side effects such as post-operative infections, complications of anesthesia and embolisms.

Low-intensity pulsed ultrasound (LIPUS) is a low-risk procedure, with skin reactions being the only side effect experienced by a very small number of patients. Patients can use the treatment independently at home, eliminating the need for repeated hospital visits. This study aims to show that LIPUS treatment is not inferior to surgical intervention by a threshold of -25 percentage points in terms of fracture healing in non-unions of the upper or lower extremity.

**Methods:**

PiNGUin will be a five-year national, prospective, controlled, randomized, open-label, multicenter study with a medical device. Patients are randomized into one of two groups: patients in the intervention group will receive daily 20-min LIPUS treatment for 200 days or undergo standard surgical intervention in the control group. Follow-up for both groups will be 12 months. The primary endpoint is fracture healing 12 months after treatment start, defined as bony consolidation of at least 3 out of 4 cortices and functional recovery. Secondary endpoints include time to fracture healing and to full weight bearing, incidence and intensity of pain, functional complaints/activities of daily living, health-related quality of life, complications, adverse events, re-operations or re-osteosyntheses and (re-) hospitalizations, hospital stays, duration and reasons for inability to work. With a one-sided significance level of 2.5%, a power of 90% and an assumed drop-out rate of 10% 184 patients will be required per treatment group.

**Discussion:**

As LIPUS is a low-complication procedure with good results to date, this treatment is considered a potential alternative to surgery. If non-inferiority is proven, patients will have a choice of both invasive and non-invasive procedures in the future.

**Trial registration:**

DRKS00034357 (German Clinical Trials Register, registered March 11th, 2025).

## Administrative information

Note: the numbers in curly brackets in this protocol refer to SPIRIT checklist item numbers. The order of the items has been modified to group similar items (see http://www.equator-network.org/reporting-guidelines/spirit-2013-statement-defining-standard-protocol-items-for-clinical-trials/).

## Introduction

### Background and rationale {6a}

A non-union is usually defined as a fracture that has not healed after 6 months and is a multifactorial, therapeutically challenging and socio-economically significant complication of fractures. Despite medical advances, non-unions occur in approximately 2–10% of all fractures and can affect up to 30% of patients with certain risk factors [1, 2]. Risk factors include exogenous factors such as open fractures or soft tissue defects and endogenous factors such as obesity, diabetes mellitus or immunosuppression. Often, the exact cause cannot be conclusively clarified. The direct and indirect costs of treatment for non-unions are significantly higher than those associated with regular bone healing [3, 4]. Non-unions often lead to a high level of suffering for patients, as they can cause persistent pain, re-hospitalizations and delayed recovery of work ability.

So far, surgical revision is considered the gold standard for treatment of non-unions. The surgical procedure depends on the type of non-union and usually requires decortication of the non-union and, if necessary, filling of bone defects with autologous/allogenous bone graft or bone graft substitutes. Autologous bone graft is the gold standard, but with the disadvantage of high donor morbidity up to 30%. Typical complications include hematoma, infection and chronic pain at the donor site [5]. Since sufficient stability is essential for bone healing, it may be necessary to extend the osteosynthesis, or even replace the material entirely, depending on the existing osteosynthesis. Various osteosynthesis procedures are available, depending on the location of the non-union. The disadvantages of surgical intervention include re-hospitalization associated with the operation and possible complications such as postoperative infections. Bony consolidation is achieved on average 200 days postoperatively but data on fracture healing rates in non-unions vary. In a review, Gebauer et al. reported fracture-healing rates of 68%−96% after non-union revision, depending on the fracture and surgical procedure and with an average fracture-healing rate of 86% [6].

The stated duration of LIPUS application until fracture consolidation varies in the individual studies [6, 16, 17]. While bony consolidation was achieved after an average of 154 days according to Nolte et al., the study by Gebauer et al. reported an average treatment duration of 168days [6, 17]. The age of the non-union has a significant influence on the duration of treatment as well [16]. In most studies, a maximum treatment duration of 200 days is sufficient and thus corresponds to the healing time after a surgical revision.

With the exception of the studies by Frankel et al. and Zura et al., there are some limitations of studies on non-unions. The number of cases is often small; in some cases, only 14 patients are reported as a case series [12, 13, 15, 18, 19]. In addition, these are exclusively single-arm studies, most of which were conducted retrospectively. The common endpoint of the studies is fracture healing, although this is not uniformly defined. Further clinical endpoints are mentioned in some studies, but again it is also not described how the endpoints were precisely defined, recorded or evaluated. Another shortcoming of the studies to date is the evaluation. In some studies, it is described that patients with insufficient compliance or treatment discontinuation were excluded from the evaluation [9, 15, 17]. As a result, the intention-to-treat principle is violated and the stated healing rates of 88% on average are probably lower. A conservative interpretation of the study results therefore assumes a fracture healing rate of 75% with LIPUS therapy [20]. According to the current literature, the fracture healing rate for treatment with LIPUS is lower than after surgical revision (75% vs. 86%), but still comparably good due to the inherent advantages of the lack of risks. In addition, the costs of LIPUS treatment proved to be significantly lower compared to surgical intervention.

The results to date in the treatment of non-unions with LIPUS are encouraging, however, the reliability of the results is still insufficient due to mentioned shortcomings of the studies.

Beyond this background, the aim of this randomized controlled study is to achieve a sufficiently high level of certainty in the results. If LIPUS treatment is proven not inferior to surgical revision, an alternative therapy will be available in the future and health insurance companies could cover the costs, which is particularly advantageous for high-risk patients.

### Objectives {7}

The study aims to show that in patients with non-unions of the upper or lower extremity, treatment with LIPUS is not inferior to surgical intervention in terms of the fracture-healing rate as primary endpoint (non-inferiority study). Fracture healing is defined as bony consolidation and functional restoration (composite endpoint).

### Trial design {8}

The study is conducted as an open, randomized controlled trial (RCT) with a medical device, designed as a non-inferiority study. Patients with non-union of the upper or lower extremity are randomly allocated in a stratified 1:1 ratio into one of two treatment groups: (1) LIPUS treatment (interventional group); treatment with LIPUS will be self-administered by the patient for 20 min per day. The total duration of treatment should be 200 days. (2) Surgical group (control group); the surgical group will serve as a control group and will receive surgical revision as by standard of care. The duration of the entire study will be five years with a recruitment period of 24 months and a follow-up period per patient of 12 months from the start of the intervention.

## Methods: participants, interventions and outcomes

### Study setting {9}

Overall, 370 patients will be recruited by 20 hospitals in Germany. The study was approved by the Ethics Committee of the Medical Faculty of the University of Duisburg-Essen (24–12,247-BO) and registered at the German Register for Clinical Trials (Deutsches Register Klinischer Studien (DRKS);

DRKS00034357): https://drks.de/search/de/trial/DRKS00034357/details.

For the preparation of the study protocol, the SPIRIT guidelines were implemented [21].

### Eligibility criteria {10}

#### Inclusion criteria

Presence of non-union after a fracture of the lower or upper extremity including the clavicleAge of fracture of ≥ 6 months and ≤ 24 monthsAge of patient ≥ 18 yearsPrimary osteosynthesis of the fractureBony defect of ≤ 1 cmClosed soft tissuesInformed consent dated and signed prior to any study activity in accordance with the International Council for Harmonization of Technical Requirements for Pharmaceuticals for Human Use (ICH)—Guideline for Good Clinical Practice (ICH-GCP Guideline) and local lawsStatutory health insurance

#### Exclusion criteria

Unstable non-union/osteosynthesisNon-union of the vertebral body or skullNon-union of the small bones of the hand and toesNon-union after osteotomyPresence of a long spiral fracture (length > 3 cm)Pathological fractures due to a malignant tumor or metastasisSurgery performed on the fracture/non-union in the last four monthsFlorid infection/osteomyelitis of non-union, exposed osteosynthesis material, soft tissue defectsTherapy with cytostaticsPacemakerPregnancy/breastfeedingPresence of comorbidity (e.g., psychiatric illness, dementia, excessive drug abuse) which, at the discretion of the treating investigator, may impair the ability to give consent, participation in the study, and compliance.Participation in another interventional study, if this impairs participation in the described study

### Who will take informed consent? {26a}

Prior to any study-related activities, a trained physician of the study team at the respective site will inform the patient about the nature of the study, all related measures and procedures, upcoming (follow-up) visits at the site and risk and benefits. Patients will be given sufficient time to ask questions or to reconsider their participation before giving written informed consent.

### Additional consent provisions for collection and use of participant data and biological specimens {26b}

No additional data or biological samples will be collected from the study patients.

## Interventions

### Explanation for the choice of comparators {6b}

Compared to single-arm studies conducted to date [6, 9–19], we aim to achieve more reliable results by including a control group. Surgical revision is considered as appropriate control intervention as it represents the gold standard in the treatment of non-unions to date. Based on previous studies, a fracture-healing rate of 86% is assumed in the surgical treatment group compared to an assumed healing rate of 75% for patients treated with LIPUS.

### Intervention description {11a}

The intervention in the study group will consist of daily 20-min treatment with LIPUS in the area of non-union using the ultrasound device. Following training in the use of the device, patients can carry out the treatment independently at home. In total, the treatment will last for at least 200 days, of which at least 180 are treatment days. For the use of the ultrasound device, patients attach a strap to the affected limb and place the probe over the marked area of the non-union. The device is equipped with a countdown timer that indicates the end of the treatment with an acoustic signal.

Patients in the control group will undergo surgical revision of the non-union. The type and extent of the operation depend on the fracture and on patient-dependent individual factors and are discussed with the patient. As a rule, the fracture ends need to be resected, the bony defect filled and the osteosynthesis has to be sufficiently stable. Autologous and allogeneic cancellous bone and various bone graft substitutes are available to fill the bony defect, as well as growth factors as additives. Various osteosynthesis procedures are also available for osteosynthesis depending on the fracture type and location (e.g., plate osteosynthesis, intramedullary nail, external fixator).

### Criteria for discontinuing or modifying allocated interventions {11b}

Study participation can be terminated upon the patient’s request, and patients may withdraw from the study for any reason at any time. Investigators may discontinue a patient’s study participation in case of health deterioration, non-compliance, intake of non-permitted medication or if an inclusion or exclusion criterion was violated after study inclusion.

For both groups, after 42 and 120 days of the respective intervention, routine imaging (X-ray or computed tomography, performed independently of the study) will be used to evaluate whether there are any signs of dynamic bone healing. If there are no signs of bone healing at all after 120 days, compared to the initial findings, these circumstances will be discussed with the patient and alternative treatment methods, including a new surgical revision, will be offered. In addition, a wait-and-see approach will be possible at this point. Routine imaging will also be performed after 200 days to confirm that at least three out of four cortices are consolidated. If the non-union is found to be healed after 200 days, no further imaging will be performed unless this is deemed necessary at the doctor's discretion at the end of the study at day 365.

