## Assignment of interventions: allocation

### Sequence generation {16a}

Randomization is carried out using the software Clincase developed by Quadratek (Berlin). In order to obtain comparable groups, randomization will be stratified by upper or lower extremity, age (≤ 60 or > 60 years) and sex in order to achieve balanced factor distributions for these relevant predictors. Other variables that could have an important influence on the primary outcome are assumed to be evenly distributed across the treatment arms by randomization. Each randomized patient will be part of the ITT analysis.

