### Plans to promote participant retention and complete follow-up {18b}

If a patient does not appear to a planned study visit, the respective study personnel will attempt to contact the patient and reschedule the missed visit as soon as possible. The patient will be informed about the importance of keeping the assigned appointment and it will be ensured whether the patient wants and/or should continue in the study. Before a patient will be classified as “lost to follow-up”, the investigator or a member of the study team must make every effort to re-establish contact with the participant (three phone calls if possible and, if necessary, writing to the participant's last known mailing address). These attempts at contact will be documented in the participant's medical record. Data collected for the patients up to the time of withdrawal from the study will be used for analysis.

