### Methods in analysis to handle protocol non-adherence and any statistical methods to handle missing data {20c}

At visit three, approximately 120 days after start of the intervention, it will be established whether the treatment has been successful. If the treatment is classified as unsuccessful for patients, the corresponding patients from both treatment groups will be offered alternative or further treatments, including (renewed) surgery. Should such additional interventions occur after visit 3, the data from visits 4 and 5 should only be viewed with caution. If analyzed according to the ITT principle, positive treatment effects of the surgical intervention could overestimate the effect of the LIPUS treatment. If patients with additional surgical intervention are counted as surgically treated, the effect of LIPUS treatment could also be overestimated, as the patients who failed and therefore underwent surgery are no longer considered in this group. If all patients with an additional procedure were excluded from the analysis, the treatment effects in both groups could be overestimated, as these patients with a failure are no longer included. For the analysis of the primary endpoint, all patients who will receive an additional surgical intervention are therefore classified as failures, as it can be assumed that the intervention was performed due to a lack of success. For the evaluation of the secondary endpoints, the last observed values before an additional surgical intervention will be carried forward (last observation carried forward (LOCF)). Because of the different interventions (non-recurring surgery vs. daily treatment with LIPUS), a smaller compliance rate in the LIPUS group will be expected, resulting in presumably lower success rates. To account for these compliance differences in the application of the treatments, the ITT population will be regarded for primary analyses. In order to estimate the differences of the treatments when applied correctly, the PP population will be analyzed additionally.

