If less than 5% of the values of the primary endpoint are missing, the primary analysis will be performed on the complete data available and a sensitivity analysis will be performed using LOCF. If at least 5% of the values are missing, the primary analysis will be performed on the basis of multiple imputation using the MAR (missing at random) assumption. The analysis on the complete data will be performed as a sensitivity analysis. Further details on the planned analyses of all endpoints and on how to deal with missing values will be defined in the statistical analysis plan.

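### Investigator-ended study participation, combined with missing-data analyses that assume ignorable loss, can raise the false non-inferiority rate if the loss falls mainly on poorly healing LIPUS patients

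*Protocol article*

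**What the plan says.** Protocol article, Criteria for discontinuing or modifying allocated interventions {11b}: besides withdrawal at the patient's own wish, the investigator can also terminate "study participation in case of health deterioration, non-compliance, intake of non-permitted medication or if an inclusion or exclusion criterion was violated". The section heading concerns the allocated intervention, but the text ends participation in the study.

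Plans to promote participant retention {18b}: "Data collected for the patients up to the time of withdrawal from the study will be used for analysis". No follow-up after withdrawal is described.

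Sequence generation {16a}: "Each randomized patient will be part of the ITT analysis". Sample size {14} likewise says that ITT serves to include patients who do not comply.

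Methods to handle non-adherence and missing data {20c} contains four relevant provisions:
- On compliance: "a smaller compliance rate in the LIPUS group will be expected, resulting in presumably lower success rates".
- Patients with an additional operation count as failures for the primary endpoint. No such rule covers patients withdrawn without an operation.
- Below 5% missing: "the primary analysis will be performed on the complete data available and a sensitivity analysis will be performed using LOCF".
- From 5% missing: "the primary analysis will be performed on the basis of multiple imputation using the MAR (missing at random) assumption", followed by "The analysis on the complete data will be performed as a sensitivity analysis". Further detail is left to the SAP.

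**The concern.** A patient taken out for non-compliance or deterioration has no month-12 DASH or LEFS score and possibly no late image, so the analysis as randomized has no observed outcome to use. Non-compliance with daily home treatment over at least 200 days arises mainly in the LIPUS arm, and the protocol links it to lower success. The decision is made by investigators who know the allocation.

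Losing likely failures from the experimental arm raises its observed healing rate. In a non-inferiority trial that works in favour of the claim. The Background {6a} makes this same criticism of earlier LIPUS studies: excluding poorly compliant patients violated ITT and probably overstated healing. Sections {11b} and {20c} together leave a similar route open here.

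**Working it through.** **Inputs.** From Sample size {14}: healing 86% (surgery) and 75% (LIPUS), margin −25 points, one-sided 2.5%, power 90%, 166 per group, 10% dropout, 184 per group, 370 in total. At the margin the true rates are 86% and 86 − 25 = 61%. The documents do not give, by arm, the share removed (d) or the healing rate among those removed (h). Both are assumptions and are varied.

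**Step 1, the plan's own figure.** n = (1.960 + 1.282)² × (0.75×0.25 + 0.86×0.14) / (0.25 − 0.11)² = 10.51 × 0.3079 / 0.0196 = 165.1, so 166 as stated. 166/0.9 = 184.4; the plan states 184, and rounding up to 185 gives 2 × 185 = 370.

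**Step 2, loss in the LIPUS arm only, complete cases.** The LIPUS rate among those remaining is s = (0.61 − d·h)/(1 − d). The chance of a false claim is Φ((s − 0.86 + 0.25)/SE − 1.96), with SE = √[s(1 − s)/(184(1 − d)) + 0.86×0.14/184].

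| d | h | s | difference (points) | SE | false-claim rate |
|---|---|---|---|---|---|
| 0 | – | 0.610 | −25.0 | – | 2.5% |
| 5% | 30.5% (half) | 0.626 | −23.4 | 0.0447 | 5.5% |
| 5% | 0% | 0.642 | −21.8 | 0.0444 | 10.8% |
| 10% | 30.5% (half) | 0.644 | −21.6 | 0.0452 | 11.3% |
| 10% | 0% | 0.678 | −18.2 | 0.0444 | 33.2% |

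A simulation of the last row gave 33.5%.

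**Step 3, which branch applies.** The 5% rule is stated without reference to arm; it is read here as the share across both arms.
- 5% loss in one arm only is 2.5% overall, so the below-5% branch applies.
- 10% loss in one arm only sits on the threshold: 18 of 370 is 4.9%, and if all 18 are LIPUS patients it is 18/185 = 9.7% of that arm.
- 10% LIPUS loss plus 5% random control loss is 7.5% overall, so the at-least-5% branch applies. The complete-case error is then about 11% (half rate) to 33% (none heal), nearly the same as without control loss.
- Multiple imputation that uses only arm and baseline covariates unrelated to healing would give about the same point estimate as complete cases.

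**Step 4, the same calculation with other loss patterns, 10% in each arm.**
- Removed patients heal at half their arm's rate: 64.4% vs 90.8%, difference −26.4 points, error 1.1%.
- None of them heal: 67.8% vs 95.6%, difference −27.8 points, error 0.4%.
- Removal unrelated to healing: 61% vs 86%, error 2.5%.

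**Step 5, would counting every missing patient as a failure repair it?** With 10% random loss in both arms the rates become 0.9 × 61 = 54.9% and 0.9 × 86 = 77.4%. The difference is −22.5 points and the error 7.5%. Scoring all missing patients as failures in both arms is therefore not a safe substitute for follow-up.

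**The case against.** Several counter-arguments carry weight.

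- **The direction is conditional.** Inflation needs loss that is related to non-healing and is more frequent or more informative under LIPUS. Step 4 shows the error falling when both arms lose patients equally and informatively. This stands, so the finding is that the error can be inflated, not that it will be.
- **A reader might infer that no planned analysis would reveal the problem.** The documents do not support that. Below 5% missing, LOCF is planned; if only LIPUS patients are lost while unhealed, LOCF would score them as failures and expose the bias. Re-operated patients already count as failures, which covers an important route for non-healing found at day 120.
- **A reader might infer that the result at planning rates already turns on this.** If 75% is the rate among completers and the missing 10% are failures, LIPUS has 0.9 × 75 = 67.5% and the lower limit is −18.5 − 1.96 × 4.30 = −26.9 points, which fails. But {14} counts incomplete healing within the 25% failures, and {6a} presents 75% as a conservative figure in view of earlier exclusions. With 75% of all randomized patients, the limit is −11.0 − 1.96 × 4.09 = −19.0 points, which passes.
- **MAR conditions on observed data.** Interim imaging, questionnaires and device-recorded compliance could enter the imputation model and reduce the bias. Those details may properly sit in the SAP.
- **Removal is optional, and other provisions soften it.** Section {11b} says investigators may do this, {11c} answers poor compliance by contacting the patient, and the endpoint committee sees the last available image. However, the protocol does not say that a withdrawn patient is scored from that image.

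The core remains. The SAP cannot recover outcomes that were not collected because participation was ended, and {20c} already names both the primary analysis and its check for the at-least-5% branch.

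**Conclusion.** The point holds in conditional form. Section {11b} conflicts with the ITT statements in {14} and {16a}. In the at-least-5% branch of {20c}, the likely one under the protocol's own 10% dropout, no named analysis addresses loss that depends on the unseen outcome.

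If the loss is confined to LIPUS and informative, the false-claim rate at the margin goes from 2.5% to about 5.5–11% (5% removed) or about 11–33% (10% removed). The upper ends require that none of those removed would have healed. The figures apply to complete-case analysis, and to imputation that adds little information about healing. Whether loss will follow this pattern cannot be settled from the documents, although {20c} makes the direction plausible. Below 5% missing, LOCF and the re-operation rule give partial protection.

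**What to change.** 1. In {11b}, separate ending the allocated treatment from ending study follow-up. All randomized patients who have not withdrawn consent keep the month-12 assessment (DASH or LEFS, and the last routine image) and are analysed as randomized, in line with {14} and {16a}. Align {18b} accordingly. This concerns data collection only and leaves the clinical grounds for stopping treatment untouched.
2. In {20c}, add to both missing-data branches a delta-adjusted tipping-point sensitivity analysis that progressively worsens the missing LIPUS outcomes, up to all failed, and reports where the non-inferiority conclusion changes.

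The cost is protocol wording and one further analysis. No extra patients are needed, and the month-12 visit is already scheduled. The sensitivity result may be less favourable to LIPUS. The content of the imputation model can stay in the SAP.
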